### Statistical analysis plan

#### Data cleaning and validation

Variable definitions will be harmonised among the three sites through consensus discussion. A common analysis protocol will be created, with the aim of standardising variables in terms of measurement units and timing of measurements. For each database, the most appropriate set of operational definitions will be applied, while considering any unique aspects of the database. Then work to standardise these definitions between each database will be undertaken. Outliers for continuous exposures and covariates will be explored. Implausible values, such as negative lipid concentrations, will be removed. The distribution of continuous variables will be compared with the known distribution from a representative population survey. Multiple imputation by chained equations will be used to address missing data of continuous covariates (for example, blood pressure) and estimates pooled according to Rubin’s rules. Baseline and follow-up lipid tests will not be imputed (see eligibility criteria).

Sites will manage data access and data curation as per local policies and guidelines. Electronic health data will be stored securely and analysed locally. Anonymised patient-level data will not be shared between sites.

#### Statistical analysis

Descriptive statistics will be used to characterise the study population. Continuous variables will be summarised using mean and standard deviation or median and interquartile range, and categorical variables will be expressed as frequency and percentage. The crude incidence rates for the outcomes of interest will be estimated, reported as cases per 1000 person years with 95% confidence intervals (CIs) derived from a Poisson or negative binomial distribution as appropriate. Time-to-event analysis using Cox proportional hazards models will be used to estimate hazard ratios with 95% CIs. The proportional hazards assumption of the Cox model will be assessed. Potential confounders will be pre-specified based on expert knowledge and available literature, and adjusted for in the model. Using the common protocol, each analysis will be run locally. Estimates for each of the three sites will then be pooled by meta-analysis using a random effects model, and heterogeneity will be estimated using *I*
^2^. All statistical analyses will be performed using either Stata, SAS, or R software.

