To compare the incidence of MACE in adults taking statins for primary prevention of CVD between HK, NZ, and the UK; andTo assess the association between LDL-C and non-HDL-C concentrations at 24 months after initiating statin therapy and MACE in adults taking statins for primary prevention of CVD, across three geographically and ethnically diverse populations.

The findings will be relevant to clinicians and organisations developing treatment guidelines worldwide.

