CDARS contains electronic health record data from the Hong Kong Hospital Authority, an integrated public healthcare system, which serves >7.4 million HK residents through 43 hospitals and institutions, 49 specialist outpatient clinics, and 73 general outpatient clinics.^18^ CDARS covers approximately 80% of all hospital admissions in HK,^19^ and has been extensively used for conducting high-quality population-based studies. Data validation has demonstrated a high-coding accuracy in CDARS.^20^

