#### Subgroup analyses

To explore heterogeneity of exposure effect, subgroup analyses will be conducted by age, sex, LDL-C categories as in the FOURIER trial^4^ (that is <0.5 mmol/l, 0.5 to <1.3 mmol/l, 1.3 to <1.8 mmol/l, 1.8 to <2.6 mmol/l, and ≥2.6 mmol/l), statin adherence prior to follow-up, statin persistence, ethnic group, and prescribed statin dose intensity.

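### Objective 1 compares MACE incidence between three countries, but the plan names only crude rates and no age- and sex-adjusted contrast between countries

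*Protocol article*

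**What the plan says.** The Introduction of the protocol article lists two objectives. The first is "To compare the incidence of MACE in adults taking statins for primary prevention of CVD between HK, NZ, and the UK". The second is the association between on-treatment lipid concentrations and MACE.

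Under Statistical analysis, incidence is covered by one sentence: "The crude incidence rates for the outcomes of interest will be estimated, reported as cases per 1000 person years", with Poisson or negative binomial confidence intervals. The section then turns to modelling: "Time-to-event analysis using Cox proportional hazards models will be used to estimate hazard ratios with 95% CIs", adjusted for prespecified confounders. On how the sites work together it says "Using the common protocol, each analysis will be run locally" and "Estimates for each of the three sites will then be pooled by meta-analysis using a random effects model". Data cleaning and validation adds "Anonymised patient-level data will not be shared between sites".

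Age and sex appear in two other places. They are in the confounder list under Covariates, and in the subgroup plan: "To explore heterogeneity of exposure effect, subgroup analyses will be conducted by age, sex". Strengths and limitations presents comparison between regions as a strength. It cautions about differences in health systems and records, but does not name demographic mix.

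**The concern.** A comparison of incidence between populations is interpretable only if the populations are alike in the main determinants of risk, or if the comparison allows for their differences. For MACE, age and sex come first among these. The plan's measure for this objective makes no such allowance.

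There is good reason to expect a different mix. The UK cohort comes from general practice records. The New Zealand cohort enters when a cardiovascular risk assessment is completed, mainly in two regions. The Hong Kong cohort comes from an integrated public hospital and outpatient system. Eligibility starts at 18 years with no upper limit, so nothing in the design forces the age distributions together.

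At stake is one of two stated objectives. The cohorts are large, so the confidence intervals will be narrow. A difference produced only by age or sex mix could look like a firm difference between countries.

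**Working it through.** **1. Does any planned analysis give an adjusted country contrast?**

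- Crude rates: no adjustment.
- Cox models: adjusted for age and sex, but fitted separately in each site. Country is constant within a site and cannot be a term in the model. The hazard ratios are for lipid concentration.
- Random-effects meta-analysis and I²: these combine the site estimates and describe their heterogeneity. They do not contrast incidence.
- Age and sex subgroups: these concern the exposure effect, not incidence by country.
- Descriptive statistics: these would show a differing mix but not remove it.

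None supplies the contrast.

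**2. The plan's own event figure** (Feasibility assessment and sample size). Inputs: about 140 000 Hong Kong patients, at least 3 years of follow-up, 10 events per 1000 person-years.

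- Person-years = 140 000 × 3 = 420 000.
- Events = 420 000 × 10/1000 = 4200. The stated figure is reproduced.

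**3. Precision of a crude rate.**

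- SE of the log rate = 1/√4200 = 0.0154.
- 95% CI = 10 × exp(±1.96 × 0.0154) = 9.70 to 10.31 per 1000 person-years, about ±3%.

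**4. Precision of a rate ratio between two countries.** Assume 4200 events in each.

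- SE of the log ratio = √(2/4200) = 0.0218.
- The 95% CI is the estimate multiplied and divided by exp(1.96 × 0.0218) = 1.044.
- Ratio detectable with 80% power = exp((1.96 + 0.84) × 0.0218) = 1.063.
- If the second country had only 1000 events, the CI factor would be exp(1.96 × √(1/4200 + 1/1000)) = 1.071.

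**5. Illustration of bias from age mix.** The article gives no age distributions and no age gradient, so every input here is assumed. Suppose two countries have identical age-specific rates, the log rate is linear in age, and ages are normally distributed with equal SD. Then crude rate ratio = (rate ratio per decade)^(difference in mean age/10).

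| Rate ratio per decade (assumed) | 2-year difference | 5-year difference |
|---|---|---|
| 1.5 | 1.08 | 1.23 |
| 2.0 | 1.15 | 1.41 |
| 2.5 | 1.20 | 1.58 |

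The true age-specific ratio is 1.00 in every cell, and rates standardised to a common age distribution would return 1.00.

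**6. Illustration of bias from sex mix.** With male shares p and q and a male-to-female rate ratio R, crude ratio = (qR + 1 − q)/(pR + 1 − p). For p = 0.45 and q = 0.55:

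- R = 1.5: 1.275/1.225 = 1.04.
- R = 2.0: 1.55/1.45 = 1.07.

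**7. Comparison.** Under these assumptions a 2-year age difference gives at least 1.08. That exceeds the CI factor of 1.044, and also the 1.071 that applies with 1000 events in the second country.

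**The case against.** The case for leaving the plan as it is has several parts.

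*The size is assumed.* This stands. The article gives no age or sex distribution for any cohort, so neither the size nor the direction of the bias can be derived. That the mix differs is a reasonable expectation from the recruitment routes, not a documented fact.

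*The article is condensed.* A common analysis protocol is to be created, and planning crude rates does not rule out standardised ones. This stands for detail such as age bands and the standard population. It does not cover the main point, because the article names the measure, and that measure does not suit the objective it must serve.

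*Crude rates are a legitimate description of observed burden, and readers will see the descriptive tables.* True, and a reason to keep them. But the objective is to compare, and a table of characteristics does not adjust the comparison. That readers will take crude differences for country effects is a prediction; that the plan offers them nothing better is a matter of record.

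*The objective is secondary in weight.* This also stands in part. The aim in the Abstract concerns only the lipid association, and the sample size rests on a hazard ratio.

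A stronger reading is tempting. Because "CDARS covers approximately 80% of all hospital admissions in HK", a reader might infer that the Hong Kong rate is understated by up to 20% and needs correcting. The article does not support this. The figure is the database's share of all admissions in the territory, not the proportion of events captured among cohort members, who supply both numerator and denominator. By the same logic, UK coverage of about 10% of the population would imply a 90% understatement there, which is absurd. Cohort members are also established users of the system, with repeat statin prescriptions and lipid tests, and MACE includes cardiovascular death. No figure for event capture in this cohort is given.

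**Conclusion.** The point holds. Objective 1 is a between-country comparison, the only incidence measure named for it is the crude rate, and no other planned analysis yields an age- and sex-adjusted contrast. Followed as written, the comparison would be confounded by any difference in age and sex mix.

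How large the confounding would be is unknown. The ratios of 1.08 to 1.20 (2 years) and 1.23 to 1.58 (5 years) rest on an assumed 1.5- to 2.5-fold rise per decade, a log-linear age gradient and equal age spread. They show that modest differences in mix could exceed sampling error; they do not predict the result.

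The change is worth making before analysis, but this is not a critical flaw. The adjusted lipid–MACE analysis and the sample size statement are untouched. No conclusion about under-capture in Hong Kong follows.

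**What to change.** For objective 1, name directly age- and sex-standardised MACE rates as the main comparison, using one common standard for all three sites (for example, the combined person-time of the three cohorts), and report between-country rate ratios with 95% CIs. Keep the crude rates beside them as descriptive. A Poisson model on the aggregated strata with country, age band and sex would be an acceptable alternative.

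Each site exports one table of events and person-years by age band (for example 5-year bands) and sex. This fits the rule that patient-level data stay at the site.

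State with the result that standardisation does not remove differences in outcome ascertainment or in health systems, so the standardised ratio is still not a pure country effect. Do not apply a correction to the Hong Kong rate based on admission coverage.

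The cost is a few sentences in the analysis plan and one aggregate table per site. No new data are needed, and the Cox models do not change.

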#### Subgroup analyses

To explore heterogeneity of exposure effect, subgroup analyses will be conducted by age, sex, LDL-C categories as in the FOURIER trial^4^ (that is <0.5 mmol/l, 0.5 to <1.3 mmol/l, 1.3 to <1.8 mmol/l, 1.8 to <2.6 mmol/l, and ≥2.6 mmol/l), statin adherence prior to follow-up, statin persistence, ethnic group, and prescribed statin dose intensity.

#### Sensitivity analyses

To assess the robustness of the primary analyses, the outcomes will be assessed based on earlier lipid test measurements, specifically at 3 months (exposure assessment window days [30, 90]; follow-up window [91, censor]) and 12 months (exposure assessment window [1, 365]; follow-up window [366, censor]) after initiating statin treatment.

The association of LDL-C and non-HDL-C as continuous exposures will be further assessed, rather than as categorical exposures.

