### Eligibility criteria

To be included in the study, each patient must meet the following eligibility criteria:

Have at least one documented baseline lipid test for total cholesterol (TC), HDL-C, and LDL-C within a year prior to index date.Have at least 12 months of clinical records after registration at the practice site (CPRD) or in the database (PREDICT).Have no previous history of atherosclerotic CVD:defined as a hospital or outpatient diagnosis of coronary heart disease (for example, myocardial infarction, ischaemic heart disease, angina, coronary artery bypass graft, percutaneous intervention), cerebrovascular disease (stroke or transient ischaemic attack), or peripheral artery disease (PAD), prior to index date; ordiagnosis of heart failure, chronic kidney disease, or diabetes with chronic kidney disease, due to their equivalent level of risk as people with established CVD, prior to index date; ora prescribing or dispensing of at least one prescription for nitrates, other antianginal drugs, peripheral vasodilators, loop diuretics, or metolazone within a year prior to index date.Be aged ≥18 years on index date.Have at least two additional statin prescriptions 1 year following index date.Have at least one documented follow-up lipid test for TC, HDL-C, and LDL-C in the year prior to the start of follow-up.

Participants who die or experience MACE before the start of follow-up will be excluded. Each participant who meets the study eligibility criteria will be entered once for analysis; duplicate entries will be removed.

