### Outcomes and follow-up

The primary outcome of interest is MACE, defined as a diagnosis of either coronary heart disease, stroke, or cardiovascular death. Secondary outcomes include all-cause mortality and the individual components of the composite MACE outcome. Follow-up will begin after the end of the exposure assessment window (24 months after prescribing or dispensing of the first statin prescription) and will end at the earliest of outcome of interest, death, disenrollment or transfer from primary care practice, or end of the analysis period (31 December 2017).

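### The 3-month sensitivity analysis starts follow-up on day 91 but admits patients on prescriptions up to day 365, so it selects on the future and builds in some immortal time

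*Protocol article*

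**What the plan says.** The Eligibility criteria section of the protocol article opens with "To be included in the study, each patient must meet the following eligibility criteria". It makes no exception for secondary or sensitivity analyses. Three of its rules look beyond the index date:

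- Prescriptions: "Have at least two additional statin prescriptions 1 year following index date". The clock runs from index.
- Follow-up lipid test: "Have at least one documented follow-up lipid test for TC, HDL-C, and LDL-C in the year prior to the start of follow-up". The clock runs back from the start of follow-up.
- Early events: "Participants who die or experience MACE before the start of follow-up will be excluded". The clock again depends on the start of follow-up.

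For the primary analysis, the Outcomes and follow-up section states: "Follow-up will begin after the end of the exposure assessment window (24 months after prescribing or dispensing of the first statin prescription"). The Sensitivity analyses section then gives two earlier versions, "3 months (exposure assessment window days [30, 90]; follow-up window [91, censor"]) and "12 months (exposure assessment window [1, 365]; follow-up window [366, censor"]). It introduces them with "To assess the robustness of the primary analyses, the outcomes will be assessed based on earlier lipid test measurements". It neither restates nor shortens the prescription rule for either version.

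**The concern.** When follow-up moves to an earlier day, the lipid-test rule and the early-event rule move with it. The prescription rule does not. In the 3-month analysis, entry is therefore decided partly by what happens after follow-up has begun.

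Take a patient who dies on day 120 before a second additional prescription. That patient fails eligibility, and the death is never counted. A patient who reaches the second additional prescription on day 200 is included, with person-time from day 91, although death before day 200 would have meant exclusion. That stretch is immortal time for all-cause death, cardiovascular death and departure from the database.

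Non-fatal coronary disease or stroke is different. It does not prevent later prescriptions, so a patient who has such an event and keeps refilling is still counted. For those events the fault is conditioning on later persistence with treatment, not strict immortality.

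What is at stake is the use of this analysis as a robustness check. Of the three lipid time points, only the 3-month one has this overlap. If its result differed from the primary result, the difference could come from the timing of the lipid test or from the selection rule, and a reader could not tell which. The Covariates section does not list adherence or refill timing among the confounders, so the planned adjustment would not remove the problem.

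**Working it through.** The article gives no figure on this point. Its one computed figure, the expected events in the Hong Kong cohort, reproduces (140 000 × 3 years × 10/1000 = 4200), but nothing below depends on it.

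**Step 1: overlap between selection and follow-up.** The prescription window closes on day 365 (Eligibility criteria). Follow-up starts on day 91 or day 366 (Sensitivity analyses), or at 24 months, about day 731 (Outcomes and follow-up).

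| Analysis | Follow-up starts | Days of follow-up inside the prescription window |
|---|---|---|
| 3-month | day 91 | 365 − 91 + 1 = 275 |
| 12-month | day 366 | 0 |
| 24-month (primary) | about day 731 | 0 |

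**Step 2: the ceiling against total follow-up.** Index dates run from 1 January 2007 to 31 December 2012, and the analysis period ends on 31 December 2017. Counted from day 91, administrative follow-up is 3927 days for the earliest index date and 1736 days for the latest. The ceiling is then 275/3927 = 7.0% and 275/1736 = 15.8%.

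**Step 3: realistic values.** Immortal time ends at the second additional prescription. If each supply lasts *s* days and refills are on time, that prescription falls on day 2*s*, and the immortal time is max(0, 2*s* − 91). The article gives no supply lengths, so *s* is an assumption shown over a range.

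| Assumed *s* | Second additional prescription | Immortal days | Share of 1736 days | Share of 3927 days |
|---|---|---|---|---|
| 28 | day 56 | 0 | 0% | 0% |
| 56 | day 112 | 21 | 1.2% | 0.5% |
| 84 | day 168 | 77 | 4.4% | 2.0% |
| 112 | day 224 | 133 | 7.7% | 3.4% |

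**Step 4: effect on a mortality ratio.** Assume a share *q* of patients reach the second additional prescription after day 90, spread evenly over days 91–365. Mean immortal time is then *q* × 137.5 days. With a constant death rate, the apparent rate over *T* days is the true rate × (1 − *q* × 137.5/*T*). For a true low-versus-high LDL-C ratio of 0.85 (the article's planned hazard ratio, borrowed here for mortality):

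apparent ratio = 0.85 × (1 − *q*_low × 137.5/*T*) / (1 − *q*_high × 137.5/*T*)

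- Equal shares (for example 0.3 and 0.3): 0.85 for every *T*, so no distortion.
- *q*_low = 0.2, *q*_high = 0.6, *T* = 1736: 0.85 × 0.984/0.952 = 0.88.
- Same shares, *T* = 3927: 0.85 × 0.993/0.979 = 0.86.
- Same shares, within days 91–365 only (*T* = 275): 0.85 × 0.90/0.70 = 1.09.

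The shares 0.2 and 0.6 are illustrative; the article has no refill data. In this illustration the whole-period effect is small and the early effect is large.

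**The case against.** The strongest reply is that this is a condensed article. The data-cleaning section leaves operational definitions to a common analysis protocol, and the study diagram is not available here. The authors may intend to adapt the prescription rule for each time point. That is possible, but the article states the rule for every patient and gives exact days for the 3-month windows. Taken together, those two statements conflict with a sound start of follow-up.

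A second reply concerns size, and much of it stands. The 275 days are a ceiling, reached only if the second additional prescription falls at the end of the year. With short supplies there may be no immortal time at all. Only deaths and exits between day 90 and that prescription are lost; later deaths count. The rule applies to every lipid group, so hazard ratios are unaffected if refill timing is the same across groups. The ratio of 1.09 in the working belongs to a period that the article does not plan to report separately.

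A reader might go further and infer two more faults.

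- Counting a year back from day 91 gives days −274 to 90, which suggests that a pre-treatment test could pass as the follow-up test. The document does not support this as a working fault. Baseline and follow-up tests are separate requirements, exposure is the latest test inside the exposure window, and that window is days 30–90. With no imputation of lipids, a patient with only a pre-treatment test has no exposure value.
- The 12-month window opens on day 1, so it admits tests on days 1–29. Because the latest test is used, such a value counts only when there is none on days 30–365.

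Neither is part of this point.

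**Conclusion.** The point holds for the 3-month sensitivity analysis only. Inclusion there depends on up to 275 days of follow-up, against none in the 12-month and primary analyses. The actual immortal time per patient lies between 0 and that ceiling, and is about 0 to 133 days under assumed supplies of 28 to 112 days.

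A reader might infer that the 3-month hazard ratios are materially wrong. The document does not show that. Bias between lipid groups requires refill timing or persistence to differ by lipid level. This is plausible, because adherence affects on-treatment LDL-C, but it is not quantified. Even under an assumed threefold difference in late refilling, a mortality ratio of 0.85 moves only to 0.86–0.88 over full follow-up. For MACE as a whole, the strictly immortal part concerns only fatal events.

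What is established is narrower: as written, the 3-month analysis is not a clean test of whether the timing of the lipid measurement matters. The primary analysis is untouched, and the repair is cheap.

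**What to change.** State the eligibility rule for each time point, and change it for the 3-month analysis in one of two ways:

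1. **Use only information available by day 90.** Drop the day-365 prescription rule for this analysis, or count only prescriptions up to day 90 with a threshold that does not exclude patients on long supplies. The threshold needs care. With a 112-day supply the first refill falls on day 112, so requiring even one further prescription by day 90 would exclude all such patients. With an 84-day supply it would exclude anyone more than six days late.
2. **Keep the day 30–90 lipid value and start follow-up on day 366.** The existing prescription rule can then stand, because the overlap is zero.

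Leave the present criterion as it is for the 12- and 24-month analyses. Because each site runs the analysis locally and patient-level data are not shared, the choice should be fixed in the common protocol before any site begins.

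The cost is about two sentences and one parameter in the common code. Under the first option the 3-month cohort differs somewhat from the primary cohort; under the second, about nine months of early follow-up (days 91–365) are given up.
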